### Study interventions

#### Evaluation

All evaluations will occur prior to the surgical intervention. The patients submitted to bariatric surgery will be evaluated again 30, 90 and 360 days following the procedure. All subjects in both groups will be submitted to the following evaluation protocol.

#### Clinical evaluation

General physical measurements and PSG will be performed a week prior to preparation for the surgery by a well-trained physician and physical therapist following recommended procedures and using precise instruments and will include body weight (kg), height (m), calculation of body mass index (BMI) using the formula weight/height^2 ^[32], circumferences (cm) of the neck, waist, and hip [33], heart and respiratory rates, blood pressure values, Mallampati index [34], tonsil index [35], the administration of specific questionnaires for sleep apnoea and excessive daytime sleepiness [36] and a quality of life questionnaire [37].

#### Educational and psychological program

During the initial evaluations, all patients will take part in an educational program in the auditorium of Santa Casa de Misericordia Hospital, where they will receive information on the development and progression of obesity, treatment (pharmacological and non-pharmacological) and the importance of regular physical activity practice. All patients will receive a chart containing the educational program [38].

#### Waist and neck circumference

The measurements of waist and neck circumference will be performed with a metric tape (7 mm in width). The sites of the measurements will be standardized. Waist circumference will be measured at the mid point between the lower edge of the last rib and the iliac crest. Neck circumference will be measured horizontally over the cricoid cartilage [39].

#### Thorax and abdomen cirtometry

Cervical thoracoabdominal cirtometry will be carried out to assess thorax and abdomen mobility and define the diaphragm index. The measurement will be performed by fixing the zero point on the metric tape to the anterior region of the thorax at the level that is being measured (axillary, xiphoid or abdominal), with the tape enveloping the entire thorax or abdomen with maximal possible pressure and the other extremity of the tape placed over this same fixed point. The aim of the maximal possible pressure of the tape on the body is to avoid the interference of soft structures in the measurements. Mobility and range of motion are provided by maximal inspiration and expiration [40].

#### Pulmonary function tests

##### Spirometry

The lung function tests will be carried out with the patient seated in a comfortable position using the KoKo PFT System Version 4.11 (nSpire Health, Inc; Louisville, CO, USA) and following guidelines for the execution of pulmonary function tests of the Brazilian Society of Pneumology [41] and the European Respiratory Society [42]. The subjects will perform the test seated as comfortably as possible, with the body erect and the upper limbs unsupported. All exams will be carried out by a technician trained in obtaining the necessary cooperation from the subjects and appropriately operating the equipment in order to ensure accurate, reproducible results. The equipment will be calibrated prior to each exam with a 3-L syringe [41].

##### Analysis of respiratory mechanics

Maximal inspiratory pressure (MIP) and maximal expiratory pressure (MEP) physiologically constitute the most adequate test for the determination of respiratory muscle strength. MIP is an indicator of ventilatory capacity and the development of respiratory failure and is indicated for the assessment of the degree of abnormality and monitoring of the weakening of inspiratory muscles individually in the progress of patients [43]. The tests will occur on the same day in which the patients undergo spirometry. The tests will be performed in a quiet setting. The patients will be seated comfortably, with the trunk at a 90-degree angle in relation to the thighs and breathing calmly and at rest [41].

##### Rebreathing test

In this study protocol, we will employ the re-inhalation method described by Read [44]. This is a simple technique that has been validated in the literature and allows the determination of the ventilatory response to CO_2 _stimulus. The patients will breathe through a mouthpiece and, after achieving a steady state, basal ventilation will be recorded for three minutes. The patients will then breathe connected to a 15-L latex balloon filled with a 7% CO_2 _and 93% O_2 _mixture for five minutes or until an end-tidal CO_2 _pressure (PetCO_2_) of 70 mm Hg is reached or until exhaustion. Data will be collected using a spirometer. The slope of ventilatory response to carbon dioxide will be obtained from a linear regression between ventilation and PetCO_2_. The data will be adjusted by a 0.9 correction factor to correct flow readings for hyperoxic gas mixture. The rebreathing tests will be carried out at Santa Casa de Misericordia Hospital (Sao Paulo, Brazil). All manoeuvres will be carried out by physicians.

##### Epworth Sleepiness Scale

The Epworth Sleep Scale is a simple, self-administered questionnaire with items addressing situations of daily activities and the occurrence of daytime sleepiness in adults. The subjects will be instructed to classify their likelihood of feeling the desire to nap or sleep in eight situations on a scale of 0 to 3 (0 = no chance of napping; 1 = small chancing of napping; 2 = moderate chance of napping; and 3 = strong chance of napping) [45,46].

##### Berlin Questionnaire

The Berlin Questionnaire is used to identify patients at high risk for sleep disordered breathing in a variety of populations. This clinical history questionnaire has recognized efficacy in distinguishing individuals at greater risk for OSA, with ten items organized into three categories: snoring and apnoea (5 items), daytime sleepiness (4 items), systemic arterial hypertension and obesity (1 item). Any marked response is considered positive. The score is divided into categories. Category 1 is considered positive when there are two or more positive responses to Items 1 to 5. Category 2 is considered positive when there are two or more positive responses to Items 6 to 8. Category 3 is considered positive when the response to Item 9 is "yes" or at BMI equal to or greater than 30 kg/m^2^. Two or more positive categories indicate high risk [47].

##### Polysomnography

A complete full-night PSG will be performed using a digital system (Embla, A10 version 3.1.2 Flaga, Hs. Medical Devices, Iceland) at the Sleep Laboratory of *Universidade Nove de Julho*. All recording sensors will be attached to the patient in a non-invasive manner using tape or elastic bands. The following physiological variables will be monitored simultaneously and continuously: four channels for the electroencephalogram (EEG) (C3-A2, C4-A1, O1-A2, O2-A1), two channels for the electrooculogram (EOG) (EOG-Left-A2, EOG-Right-A1), four channels for the surface electromyogram (muscles of the submentonian region, anterior tibialis muscle, masseter region and seventh intercostal space), one channel for an electrocardiogram (derivation V1 modified), airflow detection via two channels through a thermocouple (one channel) and nasal pressure (one channel), respiratory effort of the thorax (one channel) and the abdomen (one channel) via x-trace belts, snoring (one channel) and body position (one channel) via EMBLA sensors, and arterial oxygen saturation (SaO2) and pulse rate via an EMBLA oximeter. All PSGs will be performed and sleep stages visually scored according to standardized criteria for investigating sleep [48,49]. EEG arousals, sleep-related respiratory events and leg movements will be scored in accordance with the criteria established by the American Academy of Sleep Medicine Manual for Scoring Sleep and Associated Events [50].

The patients will be instructed to remain as relaxed as possible and sleep naturally, as if at home. All signals will be recorded continuously. Throughout the night, the subjects will be monitored by a technician experienced in polysomnography [49].

#### Bariatric surgery

Bariatric surgery will be performed on the subjects selected for the procedure at the Santa Casa de Misericórdia Hospital by experienced specialists. The surgical techniques employed for the treatment of obesity are divided into restrictive, malabsorptive and mixed. The aim of restrictive techniques (vertical gastroplasty with banding or Mason's surgery, adjustable gastric band) is to reduce gastric capacity in order to promote early satiety, thereby reducing the volume of food ingested. The aim of malabsorptive techniques (jejunoileal bypass or Payne's operation) is to reduce the absorption of foods through the exclusion of a segment of small intestine. Mixed techniques [Fobi-Capella surgery, Scopinaro's biliopancreatic diversion, and a Scopinaro technique modified by Marceau and Biron (duodenal-switch)] combine mechanical restriction to the food bolus and intestinal malabsorption [51,52].

#### Bariatric Analysis and Reporting Outcome System (Baros)

The Bariatric Analysis and Reporting Outcome System (BAROS) introduced by Oria and Moorhead in 1997 [53] provides a standard for comparisons of surgical treatment in patients with morbid obesity. This system adds or subtracts points in the evaluation of three main areas (percentage of excess weight loss, changes in medical conditions and assessment of quality-of-life), considering four outcome groups (failure, fair, good and excellent). Points are deducted for complications and reoperative surgery. The comorbidities taken into account by BAROS are hypertension, cardiovascular disease, dyslipidemia, type 2 diabetes, sleep apnoea syndrome, osteoarthritis and infertility. Idiopathic intracranial hypertension, lower extremity venous stasis disease, gastroesophageal reflux and urinary stress incontinence become comorbidities when these conditions impair or diminish quality of life or require long-tem treatment [54].

### Quality control

In order to ensure data quality, the physiotherapists and physicians in charge of the data acquisition in this study will receive specific training. Periodic external monitoring will be performed to verify the adequate application of the methodology in collecting information and performing the different examinations. The results of the preoperative and postoperative exams will be analysed by blinded evaluators.

### Statistical analysis

Data will be presented as means ± standard deviation, when applicable. For comparison of continuous variables before and after bariatric surgery, it will be used the paired Student t-test or Wilcoxon tests as appropriate. Comparisons between groups will be performed using Student *t *test or Mann-Whitney U according to the distribution.

All tests will be 2 tailed, and p values of less than 0.05 will be assumed to represent statistical significance. Multivariate linear regression will be used to identify independent predictors of the AHI following surgical weight loss. All analyses will be done using SPSS ver. 16.0 [55].

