### Aims and hypotheses

The aims of this study are to assess the evolution of pulmonary function through spirometry, ventilatory mechanics and breathing tests as well as sleep study parameters and quality of life in subjects suffering from morbid obesity undergoing bariatric surgery and determine a possible correlation between weight loss and these physiological variables. We hypothesise that the weight loss induced by surgical intervention reduces the impact of this disease on sleep quality, cardiovascular consequences and quality of life as well as financial expenditures on treatment.

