### Sample size

A previous study published by Lettieri et al. (2008) [31] identified a mean reduction in the Apnoea-Hypnoea Index of 23.4 events/hour in morbidly obese patients submitted to bariatric surgery (expected size effect). Using a standard deviation of 22.8 events/hour from the same study and considering α = 0.05 and power = 80%, the sample was estimated as 17 patients.

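### The plan does not name the randomised between-group comparison as the efficacy test or adjust it for baseline AHI; ANCOVA would be a cheap improvement.

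*Protocol article*

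**What the plan says.** The Study design and Randomisation sections of the protocol article describe a parallel-group randomised trial with a surgery group and a control group. The Statistical analysis section then fixes three things:

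- A within-arm test: "For comparison of continuous variables before and after bariatric surgery, it will be used the paired Student t-test or Wilcoxon tests as appropriate".
- A between-group test: "Comparisons between groups will be performed using Student" t or Mann-Whitney U, according to the distribution. The section does not say whether follow-up levels or changes are compared.
- A regression that looks for predictors of AHI after surgical weight loss. It is not a comparison of the randomised arms.

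One significance rule covers every test: "All tests will be 2 tailed, and p values of less than 0.05 will be assumed to represent statistical significance". No analysis is called primary, and no baseline covariate is given for the group comparison.

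The hypothesis in Aims and hypotheses is causal: "the weight loss induced by surgical intervention reduces the impact of this disease on sleep quality". Under Clinical evaluation, polysomnography takes place before surgery, so baseline AHI is available. Under Evaluation, the 30, 90 and 360-day assessments are stated for operated patients. Both groups follow the evaluation protocol, but no follow-up times are given for controls.

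**The concern.** A causal hypothesis in a randomised trial is answered by the difference between the arms. The mean change in operated patients is the effect of surgery plus whatever would have happened anyway. Under Educational and psychological program, all patients receive the same programme, so some change common to both arms is possible, and a paired test cannot remove it. The plan lists that test beside the between-group test at the same significance level and does not say which one answers the hypothesis.

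The between-group test is sound but leaves information unused. Baseline AHI is measured and is likely to be correlated with follow-up AHI. Adjusting for it narrows the confidence interval and protects against chance imbalance in a small trial.

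Letting the distribution decide between t and Mann-Whitney also leaves open what is being estimated, because the two tests address different quantities.

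**Working it through.** **Inputs from the Sample size section.** The cited study "identified a mean reduction in the Apnoea-Hypnoea Index of 23.4 events/hour in morbidly obese patients submitted to bariatric surgery (expected size effect"). The SD: "Using a standard deviation of 22.8 events/hour from the same study". Error rates: "considering α = 0.05 and power = 80"%. Result: "the sample was estimated as 17 patients". The tests are two-sided (Statistical analysis).

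**Assumptions.** Equal allocation. Baseline to follow-up correlation r of 0.3, 0.5 or 0.7, because the document gives none. The document does not say whether 22.8 is the SD of AHI levels or of change; each step below states the reading used.

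**Step 1. Reproduce 17.** Standardised effect d = 23.4 / 22.8 = 1.026.

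- Two-sample, normal approximation: n per arm = 2 × (1.960 + 0.842)² / d² = 14.9, so 15.
- Two-sample, t distribution: 15.9, so 16 per arm.
- The same divided by the Mann-Whitney efficiency of 0.955: 15.92 / 0.955 = 16.7, so 17 per arm.
- Paired: (1.960 + 0.842)² / d² = 7.5, so 8; with the t distribution 9.5, so 10.

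So 17 fits a per-arm number for a between-group comparison. It does not fit a paired test, nor a two-arm total (30 to 32).

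**Step 2. What a paired test picks up.** Take 22.8 as the SD of change, 17 operated patients, and no effect of surgery, but a fall of c in both arms. The t statistic has non-centrality (c / 22.8) × √17 on 16 degrees of freedom.

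| Common fall c (assumed), events/hour | Non-centrality | Probability that the paired test is significant |
|---|---|---|
| 5 | 0.90 | 14% |
| 8 | 1.45 | 27% |
| 10 | 1.81 | 40% |
| 15 | 2.71 | 72% |

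The between-group test keeps its 5% error rate in all four rows. No passage supports a particular c; the rows show sensitivity only.

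**Step 3. What baseline adjustment gains.** Take 22.8 as the SD of AHI at baseline and at follow-up, with 17 per group. ANCOVA multiplies the follow-up variance by 1 − r², so the effective d is 1.026 / √(1 − r²). A change score multiplies it by 2(1 − r). Non-centrality is d × √(17/2), with power from the non-central t. Using 32 or 31 degrees of freedom for ANCOVA gives the same rounded power.

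| r (assumed) | Follow-up t-test | Change-score t-test | ANCOVA | ANCOVA variance reduction against follow-up (r²) | Against change ((1 − r)/2) |
|---|---|---|---|---|---|
| 0.3 | 83% | 69% | 86% | 9% | 35% |
| 0.5 | 83% | 83% | 92% | 25% | 25% |
| 0.7 | 83% | 96% | 98% | 49% | 15% |

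ANCOVA does better than either unadjusted version at each correlation, so the gain does not depend on whether the plan meant levels or changes.

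Steps 2 and 3 read 22.8 differently. With equal variances the SD of change is 22.8 × √(2(1 − r)), which equals 22.8 only at r = 0.5. The two steps should therefore not be combined at other correlations.

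**The case against.** A reader might infer that the before-after test is the lead analysis, that surgery is tested without its control, and that baseline AHI is wasted. The document does not support any of these. The Statistical analysis section ranks nothing, and the paired test merely comes first in the text. A between-group test is planned, and Step 1 shows that 17 fits that test and not the paired one. If groups are compared on change, baseline is used, though less efficiently than by ANCOVA.

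A reader might also blame regression to the mean or night-to-night variation for a spurious fall. Eligibility rests on BMI and comorbidities, not on AHI. Without selection on AHI, these mainly add noise and do not shift the mean. What remains is a change shared by both arms, such as after the educational programme. The Background says that medical treatment gives little lasting weight loss, and falls of 8 to 10 events/hour would be 34% to 43% of the expected 23.4. The percentages in Step 2 are therefore not a forecast.

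The paired test also answers a stated descriptive aim, namely how the measures evolve in operated patients. An unadjusted t-test after randomisation is valid, and at 17 per group it has 83% power, above the 80% target. The rule for choosing a test, the scale and the time point may be settled in an analysis plan that is not shown.

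All of this stands, and it lowers the severity. It does not remove the point: the text that is shown fixes these tests, gives them equal standing, and states no adjusted comparison of the randomised arms.

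**Conclusion.** The point holds as a cheap improvement, not as a fault that must be fixed before the trial can be interpreted. The plan contains a valid between-group test, but it neither designates that test as the efficacy analysis nor adjusts it for the baseline AHI that is measured.

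The gain from adjustment is 3, 9 or 15 percentage points of power (83% to 86%, 92% or 98%). It rests on 17 being the number per group, 22.8 being the SD of follow-up AHI, equal allocation and the assumed correlations. The document does not say that 17 is per group. If it is the total, split 8 and 9, unadjusted power is only 51%.

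The within-arm test remains useful as description, but its p-value is not evidence for the effect of surgery.

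**What to change.** In the Statistical analysis section:

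1. Name one efficacy analysis: the between-group difference in AHI at one prespecified follow-up time, from ANCOVA with baseline AHI as covariate, reported with its confidence interval.
2. Fix the scale in advance (for example log(AHI + 1), with a robust or permutation p-value), in place of a choice between t and Mann-Whitney after the data are seen.
3. Use the same model for other continuous outcomes that have a baseline value. BAROS scores change and has none, so it needs an unadjusted comparison or descriptive reporting.
4. Report before-after changes within each arm descriptively, without p-values.

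In the Evaluation section, state when controls are measured, so that both arms have AHI at the chosen time point. If controls are already followed on the same schedule, this is wording only. If they are not, control follow-up visits have to be arranged, and that is the one real cost. Otherwise the change needs a little more analysis work and no new baseline measurement.

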## Methods/design

### Study design

The study design is a parallel-group randomised controlled trial and is summarised in Figure 1, and is being conducted according to the ethical standards established in the 1961 Declaration of Helsinki (as revised in Hong Kong in 1989 and in Edimburgh, Scotland in 2000). This study is registered with the World Health Organization Universal Trial Number (UTN) U1111-1121-8873, and *Registro Brasileiro de Ensaios Clínicos *(RBR-9k9hhv), and has been approved by the Human Research Ethics Committees of the Nove de Julho University, São Paulo, Brazil (process number 220506/2009). All participants gave written, informed consent.

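### The aim and visit schedule describe a course over four occasions, but the only tests named compare two time points or two groups, with no time or group-by-time term

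*Protocol article*

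**What the plan says.** The Aims and hypotheses section sets out to "assess the evolution of pulmonary function through spirometry, ventilatory mechanics and breathing tests as well as sleep study parameters and quality of life". The Evaluation section fixes the follow-up occasions: "The patients submitted to bariatric surgery will be evaluated again 30, 90 and 360 days following the procedure". With the preoperative assessment, that makes four occasions. The same section adds "All subjects in both groups will be submitted to the following evaluation protocol", but gives no follow-up days for controls. The Study design section states "The study design is a parallel-group randomised controlled trial".

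The Statistical analysis section names these methods:
- within patients: "For comparison of continuous variables before and after bariatric surgery, it will be used the paired Student t-test or Wilcoxon tests as appropriate";
- between groups: "Comparisons between groups will be performed using Student *t *test or Mann-Whitney U according to the distribution";
- a linear regression for predictors of the AHI after surgical weight loss, with no visit or time term mentioned.

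The section does not say which postoperative visit counts as the after value. It gives no analysis set and no rule for missed visits.

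**The concern.** Evolution over four occasions is a longitudinal question, and each named test handles only two columns of data. A paired test compares baseline with one later visit. A two-sample test compares the groups on one variable at one time. Nothing named estimates a trajectory, or asks whether the groups diverge over time.

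Three things are at stake. The stated aim has no analysis that answers it directly. The 30- and 90-day values contribute nothing to the 360-day estimate, although they are correlated with it. And a patient seen at 30 and 90 days but not at 360 is lost from the 360-day comparison unless the value is imputed. In a small trial each lost patient costs visible precision, and selective loss could bias the result.

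**Working it through.** **1. Aim, schedule and tests side by side.**

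| Element | Section | Occasions or columns |
|---|---|---|
| Evolution of outcomes | Aims and hypotheses | a course over time |
| Before surgery, 30, 90, 360 days | Evaluation | 4 |
| Paired t / Wilcoxon | Statistical analysis | 2 time points |
| Student t / Mann-Whitney | Statistical analysis | 2 groups |
| Linear regression | Statistical analysis | no time term named |

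Three follow-up visits can be covered by these tests only by repeating them or by leaving visits out. If each is repeated at 0.05 with 17 patients (per arm for the between-group test), the chance of at least one false positive is at most 1 - 0.95³ = 0.143 if the tests were independent. Simulation with between-visit correlation from 0.3 to 0.9 gave 0.12-0.13 for the paired tests and 0.08-0.14 for the between-group tests.

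**2. The plan's own figure.** The Sample size section gives a difference of 23.4 events/h, SD 22.8, α = 0.05, power 80% and 17 patients. A two-sample calculation with these inputs gives 15 per arm (normal) or 16 per arm (t), close to 17. A paired t-test with SD of change 22.8√2 gives 16.9, so 17. The figure is not in dispute here. The article does not say whether 17 is per arm or in total; per arm is assumed below. Two-sample power is then 83% with 17 attending per arm, 74% with 14 and 67% with 12.

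**3. Precision left unused (illustration).** Assumed, not in the document: correlation ρ of 0.5-0.7 between the 90- and 360-day values, and a fraction m of 0.2-0.3 missing at 360 days. With n patients in an arm and n_c = n(1 - m) completers:
- completers only: variance = s²/n_c;
- likelihood model using the 90-day value: variance = s²[(1 - ρ²)/n_c + ρ²/n];
- ratio = 1 - mρ².

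This gives 1 - 0.2 × 0.25 = 0.95; 1 - 0.2 × 0.49 = 0.90; 1 - 0.3 × 0.49 = 0.85. The saving is 5-15% in variance, or about 2.5-8% in standard error, before the cost of estimating the covariance.

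**4. Possible bias in a 360-day arm mean (illustration).** Same assumptions, SD 22.8.
- Odds of missing double per SD of 90-day AHI: the attenders' mean is too low by 1.5 (ρ 0.5, m 0.2), 2.1 (0.7, 0.2) or 3.0 (0.7, 0.3) events/h.
- Extreme case, in which the worst fraction m at 90 days all miss: bias = -[φ(z)/(1 - m)] × ρ × 22.8. For m = 0.2, φ(z)/(1 - m) = 0.2800/0.8 = 0.350, giving -4.0 (ρ 0.5) and -5.6 (ρ 0.7). For m = 0.3, it is 0.3477/0.7 = 0.497, giving -7.9 (ρ 0.7).

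**5. The same for the paired change.** If dropout follows the 90-day level, attenders also have lower baselines. With equal SDs, ρ(90,360) is replaced by ρ(90,360) - ρ(0,90). Taking ρ(0,90) = 0.5, a further assumption, the multiplier falls from 0.5-0.7 to 0-0.2. The biases shrink to 0-0.9 events/h (from 1.5-3.0) and 0-2.3 (from 4.0-7.9). The reduction depends on dropout following the level; dropout that followed the 90-day change itself would not be offset in this way.

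**The case against.** A reader might infer that each visit will be tested alone, in attenders only, and that the 360-day result will therefore be biased. The article supports none of this. It does not say the tests are repeated by visit, names no primary visit or 360-day between-group contrast, and gives no analysis set or imputation rule. Such rules are commonly left to a full protocol or analysis plan, which is not shown, so their absence is no finding.

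The bias figures are open to challenge as well. Dropout rate, correlation and direction of selection are all assumed. The larger figures (4.0-7.9 events/h) concern a level in one arm, so expressing them as 17-34% of the planned 23.4, which is a mean reduction, sets a level against a change. Similar dropout in both arms would largely cancel between groups. In the extreme case, no 360-day value exists above the 90-day cut-off, so a model would remove the bias only by extrapolation.

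It can also be said that evolution may be described by means and before-after contrasts, which are valid when visits are complete or missing without regard to outcome, and that a mixed model is then a matter of efficiency.

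These points stand and limit the finding. They do not remove the mismatch: the tests were named, not left open, and none of them uses the serial structure that the aim and schedule set out. A later analysis plan would have to replace that text rather than only add to it.

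**Conclusion.** The point holds as a mismatch between the aim and schedule on one side and the named tests on the other. It does not hold as a demonstrated bias. The mismatch rests on the article's wording alone and needs no assumption. Its numerical size cannot be fixed from the document, which gives no dropout rate, between-visit correlation or lead visit. The illustrations (5-15% of the variance of a 360-day arm mean; about 1.5-3.0 events/h of bias in that mean under moderate selective dropout, and less in a paired change where dropout follows the 90-day level) show the order of magnitude only. This is a worthwhile, inexpensive improvement to the analysis text.

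**What to change.** For each continuous outcome, replace the two-column tests with one repeated-measures mixed model. Include visit, baseline value, group and group-by-visit, with a within-patient covariance structure and small-sample degrees of freedom. Transform the AHI if residuals are skewed. Report the 360-day between-group contrast with its 95% CI, give the 30- and 90-day contrasts as the trajectory, and keep the simple tests as sensitivity checks.

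The group terms can be estimated only at visits where controls are also measured. The Evaluation section should therefore state whether controls are assessed at times matching 30, 90 and 360 days. If they are not, use the model for the course within the surgery group, and compare groups with a baseline-adjusted analysis at whatever follow-up time they share.

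The cost is a short rewrite of the analysis text and a clarification of the control schedule. If controls are already seen at matching times, no new data are needed. The downsides are a missing-at-random assumption that must be stated, and a covariance structure estimated in few patients.
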